### VR Intervention

The VR intervention (Reducept, the Netherlands) is a psychological VR intervention for the treatment of chronic pain. Reducept aims to teach patients that pain can be influenced and managed by changing the way they think about their pain. In the game, the user travels through the body in a spaceship (Figure 2). Along the way, the user learns about the mechanisms of pain. Reducept is based on the “explain pain” guidelines [37], which state that understanding pain and influencing the cognitive, emotional, and behavioral processes associated with it enables patients to reduce their pain experience. In addition to pain education, the user plays several serious games that stimulate the visual, auditory, and proprioceptive systems to control chronic pain through distraction and relaxation. The VR intervention uses techniques from cognitive behavioral therapy, acceptance and commitment therapy, mindfulness, and hypnotherapy [38]. The game is divided into 5 modules that build on each other and last from 5 to 10 minutes. A workbook with in-depth content on the VR modules accompanies the therapy. The planned therapy sequence consists of 6 therapy sessions of 10 to 20 minutes each.

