**Data Analysis**

Qualitative content analysis according to Kuckartz [39] will be used throughout the study to analyze qualitative data. Qualitative content analysis is a systematic and structured way of analyzing qualitative data. First, main categories are identified deductively or inductively, then text segments are systematically assigned to these categories. From these text segments, subcategories are inductively derived. This method helps to identify themes, patterns, and correlations in the data, thus providing deeper insights into the phenomenon under study. In addition, Kuckartz content analysis provides a transparent approach that increases the validity and reliability of research findings. MAX Qualitative Data Analysis (MAXQDA Plus 2022, version 22.0.1, VERBI software) will be used for the qualitative analysis.

The data related to the patients’ health outcomes are evaluated for normal distribution and sphericity, and then analyzed using repeated measures ANOVA in SPSS (version 28.0.1.0, IBM Corp).

### Phase 1

The first phase of the implementation process consists of adapting the treatment protocol of the VR intervention to the context of outpatient physiotherapy practices in Germany.

In total, 5 outpatient physiotherapy practices in Lower Saxony (Germany) will participate in the study and implement the VR intervention. At least 5 physiotherapists must work in the practices to be eligible to participate in the study. Practice managers or owners and 2 researchers will participate in guided focus groups to adapt the original treatment protocol of the VR intervention. Focus groups are a good method to investigate what participants think and why they think it [40]. In addition, the group setting can stimulate new ideas that may be hidden in individual discussions [41]. Another goal is to establish collaboration and networking among participants. The focus group guideline will be developed using the implementation outcomes of acceptability, appropriateness, adoption and feasibility [42]. The guideline will be pretested and adapted, if necessary.

The focus group will take place at the University of Applied Science and Arts in Hildesheim/Holzminden/Göttingen (Germany) and will last approximately 2 hours. One researcher will moderate the focus group, while a second researcher will take care of technical aspects, keep time, and take notes on important aspects or special incidents.

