The developed implementation strategy will be discussed with the stakeholders from the participating practices, to specify the execution of the implementation interventions. The strategy will then be executed in all 5 practices and process evaluated through an online questionnaire. The strategy will be reported according to the standards of Proctor et al [47].

Patients are eligible if they are aged 18 years or older, self-report that they have a chronic pain condition, and are able to understand and speak the German language fluently. Patients will be excluded if they have a current or previous diagnosis of epilepsy, dementia, migraine, or other neurological conditions that may prevent the use of VR or lead to adverse effects such as hypersensitivity to flashing lights or severe hearing impairment. Pain intensity, disability due to pain, fear of movement, pain catastrophizing, quality of life, and pain-related self-efficacy will be assessed using the German versions of the Numeric Pain Rating Scale [48,49], Pain Disability Index [50], Tampa Scale for Kinesiophobia [51], Pain Catastrophizing Scale [52], EQ-5D-5L (quality of life) [53], and a questionnaire assessing pain-related self-efficacy [54] before and after the VR intervention.

Physiotherapists will complete an online questionnaire to document each session of the VR intervention. The questionnaire consists of questions about the fidelity of treatment delivery based on the fidelity protocol in the study by Toomey et al [55] (eg, did the therapist adhere to the treatment protocol or which components of the treatment were delivered) and whether there were any adverse events during that session. The therapists will use the VR intervention in their practices for 6 months. Before participation in the study, written informed consent will be obtained from participants. The collected process evaluation data will be analyzed descriptively using SPSS.

### Phase 4

The final phase will be an evaluation of the overall implementation process and an analysis of the health-related outcomes of the patients.

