The evaluation of the implementation process will be done through semistructured interviews with 3 patients, 3 therapists, and 3 practice owners. Patients must have received the full treatment duration to be eligible for the interviews, therapists are included if they have treated at least 5 patients with Reducept, and 3 participants are selected from the practice owners of the participating practices. Before the interviews, all participants will complete the Acceptability of Intervention Measure, Intervention Appropriateness Measure, and the Feasibility of Intervention Measure questionnaires. The data from the questionnaires, noticeable aspects from the process evaluation in phase 3 and the implementation outcomes adoption, acceptability, appropriateness, feasibility, fidelity, and implementation costs [42] will be used to develop an interview guide. The interviews will determine the perceived effectiveness of the implementation strategy was, how the VR intervention was used in the practices, how patients perceived the use of the VR intervention and give indications how the implementation strategy can be adapted for future projects. Before use, the interview guide is pilot-tested with people from the same background who are not part of the study to ensure comprehensibility.

The interviews will be conducted online through Zoom and are expected to last approximately 60 minutes. Written informed consent will be obtained from participants before participation in the study. Interviews will be audio-recorded and transcribed verbatim. Data collection and storage will be pseudonymized. Data will be analyzed using Kuckartz’s qualitative content analysis [39].

This data will be used to adapt the implementation strategy and to create recommendations for the implementation of VR interventions for people with chronic pain in outpatient physiotherapy practices.

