### Ethical Considerations

Ethical approval for the study has been obtained from the ethics committee of the University of Applied Science and Art in Hildesheim/Holzminden/Göttingen (Germany) (April 3, 2023). The principles of the Declaration of Helsinki [56] will be strictly followed in this research project. Eligible participants will be informed of the objectives and procedures of the study. Before inclusion, written informed consent will be obtained from all patients. Participation will be voluntary, and participants will be free to withdraw from the study at any time. The reporting of this protocol follows the CONSORT (Consolidated Standards of Reporting Trials) 2010 statement: extension to randomized pilot and feasibility trials [57]. The study is registered in the German Clinical Trials Register (DRKS00030862).

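### The post score is tied to the end of the VR course and analysed by a method that needs both scores, so the patient change may mainly describe those who finished

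*Protocol article*

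**What the plan says.** - **Timing.** Methods, Phase 3 lists six patient-reported outcomes: pain intensity, pain disability, fear of movement, catastrophizing, quality of life, and "a questionnaire assessing pain-related self-efficacy [54] before and after the VR intervention". That gives one baseline and one post score. The post score is placed by reference to the intervention, with no calendar time.
- **Analysis.** Methods, Data Analysis says the patient outcomes are "evaluated for normal distribution and sphericity, and then analyzed using repeated measures ANOVA in SPSS".
- **Course and period of use.** Methods, VR Intervention: "The planned therapy sequence consists of 6 therapy sessions of 10 to 20 minutes each". Phase 1 adapts this sequence, and the article does not give the adapted number. Phase 3: "The therapists will use the VR intervention in their practices for 6 months".
- **Stopping early.** Ethical Considerations: "participants will be free to withdraw from the study at any time". Phase 3 has therapists document every session, including adverse events.
- **Full-treatment rule.** Phase 4: "Patients must have received the full treatment duration to be eligible for the interviews". This rule concerns the interviews, not the questionnaires.
- **Control.** The Limitations section acknowledges that there is no control condition.

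**The concern.** Each of the two stated choices is ordinary, but they combine badly. An assessment tied to the end of a course has no obvious date for a patient who leaves partway. An analysis that needs both scores removes any patient whose second score was not obtained. Early stopping is foreseeable, because withdrawal is free and adverse events are recorded session by session.

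If patients who stop respond differently from those who finish, the reported change is not the change among patients who started VR. No comparison group exists in which similar losses might partly offset this, so the within-patient change carries the whole bias. The Phase 4 interviews are already limited to patients who had the full treatment. If the questionnaires also reach mainly finishers, patients who stopped will be thinly represented in both sources, although a study of implementation barriers has good reason to hear from them.

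**Working it through.** The article gives no patient sample size, drop-out rate, effect size or standard deviation for these outcomes. There is no figure to reproduce. Three checks are possible.

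**1. Does the named method drop patients without a post score?**

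With two occasions there is a single within-patient difference. The repeated measures F statistic is then the square of the paired t statistic, on 1 and n − 1 degrees of freedom, where n is the number of complete pairs.

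This was confirmed on simulated data (assumed: 50 patients, each post score missing at random with probability 30%):

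- 36 patients had both scores and 14 did not.
- Repeated measures ANOVA gave F(1, 35) = 17.54. The squared paired t on the same 36 patients was also 17.54.
- The 14 others contributed nothing. The ANOVA routine used (in Python, not SPSS) refused the data set with incomplete pairs.

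With a single difference, sphericity also holds trivially, so the planned sphericity check has no function for the two assessments described.

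**2. What bias can follow?**

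Let d be the share of starters without a post score, A the mean improvement in patients with one, and B the mean improvement in patients without one.

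- Mean over all starters = (1 − d) × A + d × B
- The ANOVA estimates A
- Bias = A − [(1 − d) × A + d × B] = d × (A − B)

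As an illustration, take A = 1.5 points and let A − B run from 0 to 1.5. All of these values, and those of d, are assumptions.

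| d | A − B = 0 | 0.5 | 1.0 | 1.5 |
|---|---|---|---|---|
| 10% | 0 | 0.05 | 0.10 | 0.15 |
| 20% | 0 | 0.10 | 0.20 | 0.30 |
| 30% | 0 | 0.15 | 0.30 | 0.45 |
| 40% | 0 | 0.20 | 0.40 | 0.60 |

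For d = 30% and a difference of 1.0, the all-starter mean is 0.7 × 1.5 + 0.3 × 0.5 = 1.20, against an ANOVA estimate of 1.50. The bias is zero when d = 0 or A = B. It changes sign if those who stop have improved more.

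**3. Would changing the model alone repair this?**

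Only in part. With one baseline and one post score, a likelihood-based mixed model estimates the post mean as:

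post mean of measured patients + slope × (baseline mean of all starters − baseline mean of measured patients)

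If measured and unmeasured patients have the same baseline mean, the correction is slope × 0 = 0. The model then returns 1.50 in the example above, not 1.20. It corrects only for loss related to the observed baseline, so collecting the missing scores matters more than the choice of model.

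**The case against.** The strongest reply is that the article never says early stoppers go unmeasured. A patient who leaves after three sessions can still be assessed after that exposure. Where the authors want a full-treatment restriction they write one, and it covers only the interviews. This stands. A reader might infer that the result is a completers-only analysis by design, but the documents do not support that. The analysis is restricted to patients with a post score, who may or may not be the same people.

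A second reply is that analysis sets, missing-data rules and visit windows are commonly left to a full protocol or SAP. This also stands, and the point does not rest on their absence. It rests on the assessment anchor and the analysis method, both of which the article states.

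Three other stronger readings also fail:

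- **A specific overstatement.** If one assumes that patients without a post score do not change at all, the relative overstatement is 1/(1 − d) − 1, which is 11% at d = 10% and 67% at d = 40%. These figures only restate that assumption. In an uncontrolled design, patients who stop may also change without treatment.
- **Biased planning values for the next trial.** No section says patient change scores will be used for planning. The stated aims concern barriers, facilitators and an implementation strategy. The proposed next step is a controlled trial of that strategy.
- **Patients caught mid-course at six months.** The article does not say that enrolment runs to the last day or that outcome collection stops then.

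Finally, the session records can show attendance and adverse events among early stoppers. That helps describe them but does not supply their outcome scores.

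**Conclusion.** The point holds in limited form. The article ties the only post score to the end of the course and names an analysis that uses only patients with both scores. Patients who stop early and give no post score are therefore excluded from the sole estimate of patient change, and that estimate risks describing mainly those who finished.

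The complete-pairs mechanism is certain. Whether bias arises, in which direction and how large depends on two quantities the article does not give: the share without a post score, and how differently those patients change. Over the assumed ranges above the overstatement runs from 0 to 0.60 points, and nothing in the article places the study within that range. Patient change is not one of the two stated aims, which limits the consequence. It is still worth correcting before patients are treated, because a later SAP cannot recover scores that were never collected.

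**What to change.** 1. Set the post assessment at a fixed time after baseline, namely the scheduled end of the adapted sequence. State that it is collected from every patient who started VR, whatever number of sessions was attended. Use the session records already planned to identify early stoppers, and send them the questionnaires online or on paper.
2. Replace repeated measures ANOVA, and the sphericity check with it, by a likelihood-based mixed model on all patients with any score. State that with one post score this corrects only for loss related to the observed baseline.
3. Report the numbers started, completed, measured and lost, with reasons. Show patients who finished as a secondary description.

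The cost is a few sentences of protocol text and some reminders to patients who stop. Some of them will still not respond, which is why the counts in step 3 are needed.

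### The adverse event item is therapist-completed and limited to the session itself, and the article describes no systematic route for events between sessions or after the last one

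*Protocol article*

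**What the plan says.** All references are to the protocol article, Methods.

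- **Phase 3, who records and when:** "Physiotherapists will complete an online questionnaire to document each session of the VR intervention". The form covers fidelity of delivery and "whether there were any adverse events during that session". Process evaluation data are analysed descriptively.
- **Phase 3, patient measures:** six constructs (pain intensity, disability, fear of movement, catastrophizing, quality of life, self-efficacy) are assessed "before and after the VR intervention".
- **VR Intervention, exposure:** "The planned therapy sequence consists of 6 therapy sessions of 10 to 20 minutes each". This is the original sequence. Phase 1 adapted the treatment protocol, and the article does not give the adapted version.
- **Phase 3, duration of use:** "The therapists will use the VR intervention in their practices for 6 months". This is the period of use in the practices, not follow-up per patient.
- **Phase 4, interviews:** "semistructured interviews with 3 patients, 3 therapists, and 3 practice owners". For patients there is a condition: "Patients must have received the full treatment duration to be eligible for the interviews". One stated topic is "how patients perceived the use of the VR intervention". Adverse events are not named as a topic.

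**The concern.** The study chose to collect adverse events, and its exclusion criteria show that it expects some patients could be harmed by VR. The item it describes nevertheless has a window that closes when the session closes. Effects that start later, such as nausea or dizziness that evening or a pain flare the next day, are not asked about. If such an event makes a patient stay away, there is no later session and so no later form. The rule for the patient interviews then leaves that patient out as well.

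Both gaps push the count downwards. The results are meant to yield recommendations for using VR in outpatient practices and to be a starting point for later randomized studies. A low count could be read there as good tolerability overall, when it would speak only to what therapists saw or heard during sessions.

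**Working it through.** The article states no adverse event rate, patient number or dropout rate, so there is no planned figure to reproduce. The check has two parts.

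**1. Length of the window.** Inputs from VR Intervention: 6 sessions, 10 to 20 minutes each.

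- Shortest: 6 × 10 = 60 minutes per patient.
- Longest: 6 × 20 = 120 minutes per patient.

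Six sessions leave 6 − 1 = 5 intervals between sessions, plus the time after the last one. None of these falls within the item as worded. The article does not state session frequency, so the length of the intervals is unknown.

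**2. Each described route, set against each kind of event.**

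| Route in the article | Event during a session | Event between sessions or after the last | Delayed event that keeps the patient away |
|---|---|---|---|
| Therapist's session form (Phase 3) | Asked | Not asked; known only if the patient volunteers it and the therapist records it | No later form exists |
| Six patient scales, pre and post (Phase 3) | Not an adverse event item | A lasting worsening of pain or disability could show in the score, but not as an identified event; transient nausea or dizziness would leave no identifiable trace | Nothing to see unless the post measures are completed |
| Patient interviews (Phase 4, 3 patients) | Not a named topic | Might be mentioned | Excluded by the full-treatment rule |
| Therapist and practice owner interviews (Phase 4, 3 each) | Not a named topic | Might be mentioned second-hand | Might be mentioned second-hand |

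The Phase 4 interview guide draws partly on what stands out in the Phase 3 process data. An event that the session form did not ask about is therefore unlikely to prompt an interview question by that path.

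Only the first cell of the table is a systematic adverse event question. The other entries depend on someone happening to raise the matter, or do not identify an event at all.

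**The case against.** **This is a condensed article.** Definitions, reporting windows and withdrawal records usually sit in the full protocol, and the form itself is not shown. This stands as far as it goes: one cannot conclude that no other safety procedure exists. But the point does not rest on silence alone. The article states a window for its one adverse event item, and that window is too narrow for the effects one would want to know about.

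**Safety is not an aim.** The aims are barriers, facilitators and an implementation strategy, and the item belongs to descriptive process data. A count correctly labelled as in-session would be accurate. This also stands. It limits how serious the point is and is the reason labelling is the minimum remedy.

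A reader might also infer three stronger claims, none of which the documents support.

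- *That events ending participation are never recorded.* An event during a session that makes the patient stop falls within that session's form. Only events arising afterwards can slip through, and a returning patient may still volunteer one.
- *That the plan breaks its own safety criterion.* Phase 3 does list side effects or safety, but as a criterion for choosing implementation interventions such as training or modeling. That choice is made before the 6 months of VR use, so session data could not feed it.
- *That the shortfall can be given as a percentage.* That would need an assumed session frequency or patient number. A share of elapsed time is also not a share of events missed, because risk may cluster near exposure.

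**Conclusion.** The point holds in a limited form. As described, adverse event counts will be in-session and therapist-recorded, drawn from 60 to 120 minutes per patient under the original session sequence. No systematic route is described for events between sessions or after the last one, or for a delayed event that keeps a patient from returning. The expected direction of error is under-counting; its size cannot be derived from the article.

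This rests on two assumptions: that the form's wording matches the article's summary of it, and that the full protocol adds no other route. If either is wrong, the point shrinks to a reporting clarification. It affects the safety description of a single-group pilot. It touches no error rate, sample size or stated aim. It is worth acting on because the remedy is so cheap.

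**What to change.** 1. Reword the session item along the lines of: *any adverse event during this session or since the previous session (ask the patient)*, with the two periods ticked separately.
2. Add the same item to the existing post-intervention patient assessment, so that the time after the last session is covered up to that assessment. The article does not say how soon after the last session the assessment takes place. If it is on the same day, this item will add little.
3. Report in-session and between-session events separately, per patient.
4. At minimum, if the form cannot be changed, label the counts in every report as in-session, therapist-recorded events.

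Cost: the wording of one item, one added item on an assessment that already takes place, and about a minute per session. Only data capture changes, not treatment. One gap remains: a patient who neither returns nor completes the post-intervention assessment is still not asked, and the report should say so.
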